## Recruitment

|                                     |           |                           |            |      |
|-------------------------------------|-----------|---------------------------|------------|------|
| Recruitment status                  |           | Completed                 |            |      |
| Date of first participant enrolment |           |                           |            |      |
| Anticipated                         | 1/05/2021 | Actual                    | 4/07/2021  |      |
| Date of last participant enrolment  |           |                           |            |      |
| Anticipated                         | 1/06/2021 | Actual                    | 30/08/2021 |      |
| Date of last data collection        |           |                           |            |      |
| Anticipated                         | 1/06/2021 | Actual                    | 30/08/2021 |      |
| Sample size                         |           |                           |            |      |
| Target                              | 1398      | Accrual to date           | Final      | 1505 |
| Recruitment in Australia            |           |                           |            |      |
| Recruitment state(s)                |           | ACT,NSW,NT,QLD,SA,TAS,VIC |            |      |

## Ethics approval

---

|                                               |                                                                                                                                                     |
|-----------------------------------------------|-----------------------------------------------------------------------------------------------------------------------------------------------------|
| Ethics application status              | Approved                                                                                                                                            |
| Ethics committee name [1]              | University of Sydney Human Research Ethics Committee                                                                                                |
| Ethics committee address [1]           | Research Integrity and Ethics Administration   Research Portfolio
[name] |
| Ethics committee country [1]           | Australia                                                                                                                                           |
| Date submitted for ethics approval [1] | 16/11/2020                                                                                                                                          |
| Approval date [1]                      | 24/02/2021                                                                                                                                          |
| Ethics approval number [1]             | 2020/858                                                                                                                                            |

## Summary

---

|                      |                                                                                                                                                                                                                                                                                                                                                                                                                                                                                                                                                                                                                                                                                                                                                                                                                                                                                                                                                                                                                                                                                                                                                                                 |
|----------------------|---------------------------------------------------------------------------------------------------------------------------------------------------------------------------------------------------------------------------------------------------------------------------------------------------------------------------------------------------------------------------------------------------------------------------------------------------------------------------------------------------------------------------------------------------------------------------------------------------------------------------------------------------------------------------------------------------------------------------------------------------------------------------------------------------------------------------------------------------------------------------------------------------------------------------------------------------------------------------------------------------------------------------------------------------------------------------------------------------------------------------------------------------------------------------------|
| Brief summary | 
This study is investigating how different formats of information provision on breast density affect women's screening intentions, psychological outcomes and knowledge of breast density.
 
Who is it for?
You may be eligible for this trial if you are female, aged 40-74 years, live outside Western Australia and have no prior history of breast cancer or ductal carcinoma in situ.
 
Study details
Participants in this study will complete an online questionnaire and during which will be presented with a hypothetical scenario of undergoing a routine screening mammogram and receiving the results.
Participants will be randomised to receive control information (screening mammogram result without the breast density messaging) or one of two versions of the intervention with breast density information via notification messaging. Participants will then be asked to complete questions in response to the information they have received.
 
It is hoped this study will inform researchers of how different formats of information on breast density impact women's screening intentions and psychological outcomes.
 |
|----------------------|---------------------------------------------------------------------------------------------------------------------------------------------------------------------------------------------------------------------------------------------------------------------------------------------------------------------------------------------------------------------------------------------------------------------------------------------------------------------------------------------------------------------------------------------------------------------------------------------------------------------------------------------------------------------------------------------------------------------------------------------------------------------------------------------------------------------------------------------------------------------------------------------------------------------------------------------------------------------------------------------------------------------------------------------------------------------------------------------------------------------------------------------------------------------------------|

**Data sharing statement**

---

**Will individual participant data (IPD) for this trial be available (including data dictionaries)?**

No

In line with our ethics approval, participant data will be made anonymous and will be aggregated for the purpose of statistical analyses. Findings will be reported at the group/condition level rather than the individual participant level.

No/undecided IPD sharing reason/comment

No other documents available

**What supporting documents are/will be available?**

No

**Summary results**

---

**Have study results been published in a peer-reviewed journal?**

Other publications

---

Have study results been made publicly available in another format?

## Statistical analysis plan

**Working title:** Australian women's intentions and psychological outcomes related to breast density notification and information with mammography screening results: An online randomized experiment

**Broad aims:** This study aims to quantitatively assess how information provision of breast density information affects women's intention to seek supplemental screening and self-reported psychological outcomes.

### Outcome measures:

Variable name in SPSS in *light blue*

Variable for comparison: condition (*condition*)

Primary outcomes:

- intentions to seek supplemental screening (*Intent\_Screen\_SuppScreen*)
- psychological outcomes
  - feeling anxious (*Anxiety*)
  - feeling informed (*Informed*)
  - feeling confused (*Confusion*)
- breast cancer worry (*CancWorryAfter*)

Secondary outcomes:

- intention to speak to a GP (*Intent\_TalkGP*)
- breast density knowledge
  - Knowledge about percentage (*BDKnowl\_Percentage*)
  - Knowledge about cancer risk (*BDKnowl\_CancRisk*)
  - Knowledge about masking (*BDKnowl\_Masking*)
  - Knowledge about age (*BDKnowl\_Age*)
- Cancer risk perception (*Percep\_CancRisk*)

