**Description of intervention(s) /exposure**

This study aims to quantitatively assess how different formats of information provision on breast density affect women's screening intentions, psychological outcomes (anxiety and breast cancer worry) and knowledge of breast density.

This study will use a 3-arm randomised trial design. This trial will be conducted online through a survey platform. An online sample of Australian women (outside of Western Australia) will be recruited through a large market research organisation. Women will be aged between 40 to 74 years with no prior history of breast cancer or ductal carcinoma in situ (DCIS). Women will not be required to have undergone screening mammogram prior to participating in this study.

Women will be presented with a hypothetical scenario in which they were asked to imagine going for a routine mammogram screening and receiving a letter about their mammogram results. Women then will be randomised to be shown one of three example letters (written format) about mammography results.

Arm 1: Control group (standard screening mammogram result)

Women in the control group will be shown a standard screening mammogram result letter, which will show a "clear" result, i.e., no breast cancer could be seen on the mammogram. This letter will be similar to the ones that breast screening services in Australia send out to women with 'clear' results.

Arm 2: Intervention 1 (standard screening mammogram result + existing breast density notification messaging (e.g. WA))

Women in the intervention 1 will be shown the same letter as the control group, along with an additional breast density notification letter for women with dense breasts. This breast density letter will be identical to the ones that screening services in Western Australia send out to women who are found to have dense breast tissue. This letter includes information that the woman's breast tissue is dense, followed by information on what breast density means, its implications and following up with a GP.

Arm 3: Intervention 2 (standard screening mammogram + health literacy sensitive breast density messaging)

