| Statistical methods / analysis                                                                     | The proposed sample (n=1398) provides 80% with an adjusted alpha of 0.025 to account for multiple comparisons between either intervention arm and the control. Statistical analysis will be conducted using planned contrasts between intervention arms and control and implemented in regression models. All data will be analysed by researchers at the University of Sydney and compiled for publication and dissemination. |

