### Specific research questions:

1. Do outcomes relating to intention to seek supplemental screening, feelings of being anxious, informed or confused, breast cancer worry, breast density knowledge, cancer risk perception and intention to speak to a GP differ between women who received screening mammography results with or without breast density messaging?
2. Do outcomes relating to intention to seek supplemental screening, feelings of being anxious, informed or confused, breast cancer worry, breast density knowledge, cancer risk perception and intention to speak to a GP differ between women who received existing breast density notification messaging and health literacy sensitive breast density messaging?
3. Do women's breast cancer worry differ before and after the breast density notification?  
Does the difference vary depending on which messaging they receive?
  - Intervention (*condition=2* or *condition=3*)
  - Cancer worry before intervention (*CancWorryBefore*)
  - Cancer worry after intervention (*CancWorryAfter*)

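### No baseline covariate is named for the between-arm comparisons of post-letter worry, although a baseline worry score is collected; adjusting for it would add precision

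*Combined protocol and SAP*

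**What the plan says.** The SAP, under Outcome measures, lists "breast cancer worry (*CancWorryAfter" among the primary outcomes. The only analysis variable it names there is given as "Variable for comparison: condition". In the registry record, primary outcome 3 is a single 4-point worry item with one time point, immediately after the letter.

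Under Specific research questions, questions 1 and 2 ask whether worry and the other outcomes differ between arms. Neither names a covariate. Question 3 concerns worry before against worry after, and whether that difference depends on the message. It is the only place where the baseline item appears, as "Cancer worry before intervention (*CancWorryBefore", and the conditions listed with it are 2 and 3.

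On method, the registry record (Study design, Statistical methods / analysis) says only that the analysis will use "planned contrasts between intervention arms and control and implemented in regression models". It does not give the type of regression or the covariates.

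**The concern.** A measurement of the same construct, taken before the letter, is an obvious candidate covariate for the post-letter score. If it is left out, the variation in post-letter worry that baseline worry could explain stays in the residual. Chance differences between arms in baseline worry then remain part of the sampling error of the estimated effect, and the confidence interval on a primary outcome is wider than it need be.

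The one planned use of the baseline does not fill the gap. Question 3 lists the two notification arms only, whereas the sample size and the alpha of 0.025 are set for each notification arm against control.

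There is a second, smaller cost. With the covariates unstated, both an adjusted and an unadjusted result are compatible with the plan, and the choice between them could be made after the data are seen.

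**Working it through.** **Inputs from the documents**
- Total sample 1398 and 80%, from "The proposed sample (n=1398) provides 80% with an adjusted alpha of 0.025". The 80% is read as power.
- Alpha 0.025, set as an "adjusted alpha of 0.025 to account for multiple comparisons between either intervention arm and the control".
- Three arms.

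**Assumptions, because the documents are silent**
- Equal allocation, so 1398 / 3 = 466 per arm.
- A two-sided test, so the critical value is 2.241.
- An effect of 0.20 SD.
- A before/after correlation r of 0.3, 0.5 or 0.7, with a linear model.

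**Step 1: the plan's own figure.** The total of 1398 cannot be reproduced, because no effect size, SD or event rate is stated. Solving backwards, the detectable difference at 80% power is (2.241 + 0.842) × √(2/466) = 3.083 × 0.0655 = 0.202 SD. An effect of exactly 0.20 SD would need 476 per arm, or 1428 in total. An assumed effect of 0.20 SD is therefore close to what the sample can detect.

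**Step 2: unadjusted power.** Power = Φ(0.20 / √(2/466) − 2.241) = Φ(3.053 − 2.241) = Φ(0.812) = 79%.

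**Step 3: power with baseline adjustment.** In a linear model the variance of the contrast is multiplied by 1 − r², so power = Φ(3.053 / √(1 − r²) − 2.241).

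| Assumed r | Variance factor | Narrower interval | Equivalent women per arm, unadjusted | Power |
|---|---|---|---|---|
| none | 1 | – | 466 | 79% |
| 0.3 | 0.91 | 4.6% | 466 / 0.91 = 512 | Φ(3.200 − 2.241) = 83% |
| 0.5 | 0.75 | 13.4% | 466 / 0.75 = 621 | Φ(3.525 − 2.241) = 90% |
| 0.7 | 0.51 | 28.6% | 466 / 0.51 = 914 | Φ(4.275 − 2.241) = 98% |

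**Step 4: does the gain survive a 4-point item?** Both scores were simulated as correlated normal variables and cut to four categories with assumed shares of 30%, 40%, 20% and 10%. There were 466 per arm, a shift of 0.215 SD on the underlying scale, a linear model, and 1500 runs per case.

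| Underlying r | Correlation of the 4-point scores | Power, unadjusted | Power, adjusted | Ratio of standard errors |
|---|---|---|---|---|
| 0.3 | 0.26 | 78% | 80% | 0.966 |
| 0.5 | 0.44 | 80% | 87% | 0.899 |
| 0.7 | 0.62 | 80% | 96% | 0.783 |

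Coarse scoring lowers the correlation and so the gain, but the direction holds. The standard error ratios are close to √(1 − r²) evaluated at the correlation of the 4-point scores. For example, √(1 − 0.44²) = 0.898.

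**The case against.** The strongest objection is that the plan never says the comparison is unadjusted. Condition as the variable for comparison identifies the exposure and need not be the whole model, and the registry record does refer to regression. This stands. A reader might infer that the trial has committed to an unadjusted analysis, but the documents support only that no covariate is specified.

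Two other strong readings are also unsupported. A reader might take question 3 to mean a comparison of change scores, which would itself be inefficient. The SAP names no method there, and a baseline-adjusted or repeated-measures model would answer the question equally well. A reader might also extend the point to Anxiety. The documents show no baseline version of that item and no correlation with baseline worry, so no gain can be put on it.

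The size of the gain is uncertain. The correlation is not in the documents, and the outcome is a reaction to a hypothetical letter, so a high correlation cannot be presumed. At 0.3 the gain is modest. The factor 1 − r² belongs to a linear model, and the regression type is unstated. The registry gives a final sample of 1505, about 502 per arm if equal. The same formula then gives Φ(0.20 / √(2/501.7) − 2.241) = 82% unadjusted, which leaves a little less to gain.

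Finally, the baseline item is listed only beside conditions 2 and 3, and nothing confirms that the control arm was asked it. The registry record also shows data collection ended on 30/08/2021, so timing affects how an adjusted analysis may be described. These points limit the size and labelling of the gain but do not remove it.

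**Conclusion.** The point holds as a gap in specification with a cost in precision. A baseline worry score is collected, post-letter worry is a primary outcome, and nothing in the plan brings the two together for the contrasts with control. Validity is not in question, because randomisation protects the unadjusted comparison from bias.

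The benefit of adjustment runs from about 4 percentage points of power at an assumed correlation of 0.3 to about 19 at 0.7 (79% to 83%, and 79% to 98%). It is somewhat smaller once both scores are on four categories. These figures rest on equal arms, a two-sided alpha of 0.025, an assumed effect of 0.20 SD and a linear model. They apply to the contrasts with control, since the plan gives no alpha for the comparison of the two messages. The change is worth making but does not decide whether the trial is sound.

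**What to change.** First confirm whether CancWorryBefore was asked in all three arms.

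- **If it was:** state in the SAP that the regression models for CancWorryAfter include CancWorryBefore as a covariate for all contrasts, including those with control.
- **If it was not:** adjust only the contrast between conditions 2 and 3, and say so.
- **In either case:** name the type of regression, report the unadjusted result as a sensitivity analysis, and use the same adjusted model for the part of question 3 that compares the two messages.

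The cost is a sentence or two in the SAP, with no new data if every arm answered the item. There is one small downside: in an ordinal or logistic model the odds ratio becomes conditional on baseline worry, so marginal differences should be reported beside it. If outcomes have already been examined by arm, the adjusted analysis should be labelled as added afterwards.

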### Specific research questions:

1. Do outcomes relating to intention to seek supplemental screening, feelings of being anxious, informed or confused, breast cancer worry, breast density knowledge, cancer risk perception and intention to speak to a GP differ between women who received screening mammography results with or without breast density messaging?
2. Do outcomes relating to intention to seek supplemental screening, feelings of being anxious, informed or confused, breast cancer worry, breast density knowledge, cancer risk perception and intention to speak to a GP differ between women who received existing breast density notification messaging and health literacy sensitive breast density messaging?
3. Do women's breast cancer worry differ before and after the breast density notification?  
Does the difference vary depending on which messaging they receive?
  - Intervention (*condition=2* or *condition=3*)
  - Cancer worry before intervention (*CancWorryBefore*)
  - Cancer worry after intervention (*CancWorryAfter*)

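### Questions 2 and 3 of the SAP both examine the condition 2 v condition 3 effect on breast cancer worry; the plan should name one deciding analysis, adjusted for the baseline worry score it already collects.

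*Combined protocol and SAP*

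**What the plan says.** Under Specific research questions, question 2 asks whether a list of outcomes that includes breast cancer worry will "differ between women who received existing breast density notification messaging and health literacy sensitive breast density messaging". That is condition 2 against condition 3. Question 3 is restricted to those two conditions and names two variables, CancWorryBefore and CancWorryAfter. Its first part asks whether worry changes from before to after the notification. Its second part asks: "Does the difference vary depending on which messaging they receive".

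Under Outcome measures, the worry entry in the primary list is "breast cancer worry (*CancWorryAfter", the post-letter score. The registry record agrees: its third primary outcome is worry after the letter, measured immediately after the intervention. Neither the SAP's outcome lists nor the registry's contain CancWorryBefore or a change score.

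The only statement on error rates is in the registry record, Study design. It says that the sample "provides 80% with an adjusted alpha of 0.025 to account for multiple comparisons between either intervention arm and the control". The analysis there is "planned contrasts between intervention arms and control and implemented in regression models". Neither sentence mentions condition 2 against condition 3.

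**The concern.** CancWorryBefore is measured before the letter is shown, so randomisation makes its expected difference between conditions zero. On a mean-difference scale, the contrast in post-letter worry (question 2) and the contrast in before/after change (second part of question 3) therefore estimate the same quantity: the effect on worry of one letter relative to the other. The SAP lists them as separate numbered questions. It gives no model for question 3, no ranking of the two, no alpha for this contrast, and no reading for the case where one is significant and the other is not.

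Two things are at stake. If either result could be put forward as the finding, one randomised effect has two chances to reach significance. And if question 2 is answered without the baseline score, the trial gives up precision for which it has already collected the data.

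**Working it through.** **Inputs from the documents.** Adjusted alpha 0.025, power 80% and n = 1398 (registry record, Study design). Three arms. Worry is a single item with a 4-point response scale.

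**Inputs assumed.** The documents give no before/after correlation ρ, no SDs, no model for question 3 and no alpha for condition 2 v condition 3. I take ρ from 0.3 to 0.8, equal SDs before and after, tests on mean differences, and two-sided 0.025 per test, borrowed from the comparisons with control.

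**The plan's own figures.** If the unadjusted level is 0.05, then 0.05/2 = 0.025. The sample size cannot be rebuilt from the documents alone because no effect size is given. It does follow from one assumed scenario, 50% v 60%: (2.2414 + 0.8416)² × (0.25 + 0.24)/0.10² = 9.505 × 49 = 465.7, so 466 per arm, and 3 × 466 = 1398. Nothing here suggests that the sample size is wrong.

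**Step 1: how closely the two tests are tied.** With common variance σ², cov(post, post − pre) = σ²(1 − ρ) and var(post − pre) = 2σ²(1 − ρ).
- Raw post score v change score: correlation = (1 − ρ)/√(2(1 − ρ)) = √((1 − ρ)/2).
- Raw post score v baseline-adjusted post score: correlation = √(1 − ρ²).

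**Step 2: chance of at least one false positive.** This is 1 − P(|Z1| < 2.2414, |Z2| < 2.2414) for a bivariate normal with the correlation from step 1.

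| ρ | Question 3 as change score: correlation | At least one false positive | Question 3 baseline-adjusted: correlation | At least one false positive |
|---|---|---|---|---|
| 0.3 | 0.592 | 0.0451 | 0.954 | 0.033 |
| 0.5 | 0.500 | 0.0465 | 0.866 | 0.038 |
| 0.8 | 0.316 | 0.0483 | 0.600 | 0.045 |

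Against 0.025, the ratios are 1.80 to 1.93 for a change score and 1.3 to 1.8 for a baseline-adjusted test. At 0.05 per test the change-score figures are 0.088 to 0.095.

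The equal-SD assumption matters. At 0.05 per test, a baseline SD 0.7 times the post-letter SD gives 0.077 to 0.083 (about 1.5 to 1.7 times), and 1.3 times gives 0.087 to 0.097 (ρ from 0 to 0.9 in both cases).

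**Step 3: differing verdicts under a true effect.** Give the raw post-score test 80% power, so its noncentrality is 2.2414 + 0.8416 = 3.083. The change-score noncentrality is 3.083/√(2(1 − ρ)). By simulation, exactly one of the two tests is significant in about 28% of trials at ρ = 0.3, 23% at 0.5 and 20% at 0.8. In 1,000,000 simulated trials at each ρ, the two were never both significant in opposite directions.

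**Step 4: what baseline adjustment gains.** Power = Φ(3.083/√(1 − ρ²) − 2.2414).
- ρ = 0.3: Φ(3.232 − 2.241) = 0.84
- ρ = 0.5: Φ(3.560 − 2.241) = 0.91
- ρ = 0.8: Φ(5.138 − 2.241) = 0.998

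The raw post score has 0.80 throughout. The change score has Φ(2.606 − 2.241) = 0.64 at ρ = 0.3 and Φ(4.875 − 2.241) = 0.996 at ρ = 0.8. Adjustment is at least as powerful as either across this range.

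**The case against.** The strongest reply is that the plan already implies an order. CancWorryAfter is the primary worry outcome in the SAP and the registry record, and a change score is in no outcome list. A reader might infer that nothing decides between the two analyses and that a significant change-score result could be reported as a finding on a primary outcome. The documents do not support that. If the post score leads and question 3 is supportive, the primary test keeps its level.

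This stands, but it leaves part of the gap open. CancWorryAfter enters both questions, so naming it does not say whether it is analysed raw, as change, or adjusted for baseline. Question 3 carries no label marking it as supportive or exploratory.

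A second reply is that the change-score test is itself an inference. The SAP poses a question and lists two variables, while the registry record speaks of regression models. Regressing the post score on condition and baseline fits that wording equally well and gives the smaller figures in step 2. This also stands.

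Third, the two contrasts coincide only for mean differences. The worry item has four ordered categories and the model scale is not stated. Under an ordinal or dichotomised model, the effect on the post score and the effect on change need not be the same quantity. That is correct, and it is a further reason to name the model.

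Finally, differing verdicts here mean one test significant and the other not. At ρ = 0.8 the 20% is essentially the raw post-score test's own 20% miss rate, because the change-score test almost always rejects.

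**Conclusion.** The point holds as a clarification that also improves the method at no data cost. The SAP addresses one randomised effect on worry in two numbered questions. It does not relate the two answers, state an alpha for the contrast, or say whether question 2 uses the baseline score.

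A reader might infer that the false-positive rate nearly doubles, or that the two answers could contradict each other. Neither is established. The increase arises only if either result may support a claim, a reporting rule the documents do not contain. Its size depends on a model, a correlation and variances that are all assumed: 0.045 to 0.048 for a change score, and 0.033 to 0.045 if question 3 is baseline-adjusted, against 0.025. Significance in opposite directions is not a realistic outcome.

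The firmer result does not depend on multiplicity. For correlations of 0.3 to 0.8, a single baseline-adjusted test has power 0.84 to 0.998 where the raw post score has 0.80, and it removes the 20% to 28% of trials in which the raw post score and a change score would give different verdicts with no written way to read them. These powers are normal approximations for mean differences on a 4-point item.

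**What to change.** For condition 2 v condition 3, make the deciding worry analysis a regression of CancWorryAfter on condition with CancWorryBefore as covariate. State the model scale and the alpha for this contrast. Let that one analysis answer both the worry part of question 2 and the second part of question 3. Label any between-arm change-score test as supportive. Keep the first part of question 3, the within-arm before/after comparison, as planned: it is a separate question, and nothing above argues against it.

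The cost is a few sentences in the SAP. No new data are needed, since CancWorryBefore is already one of the SAP's variables, and a regression fits the framework in the registry record. The only loss is that a between-arm change-score test could no longer carry a claim by itself. The Recruitment section records data collection as ended on 30/08/2021, so the change must be accompanied by a statement of whether it was decided before or after the data were seen.
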